### Statistical methods

Most analyses will follow the intent-to-treat principle. The last-observation-carried-forward method will be used to impute missing data to maintain the integrity of the data set. Data will be analyzed using Stata MP 13.0 and SPSS 21.

### Primary analysis

The data will be analyzed using linear regression including terms for the healthy family lifestyle and family recreation service-integration approaches, their interaction and, where appropriate, time (a repeated measure). If the distribution of the primary outcome is right-skewed and cannot be transformed to a normal distribution, Poisson regression will be used. Estimates and corresponding 95% confidence intervals will be reported. The income group (Income Support vs. other source program) and the age of the focus child corresponding to strata variables in randomization will be included in the model.

Analysis of the FSI and quality of life data will be guided by the Canadian guidelines for the economic evaluation of health technologies [98], which comprises a five-part analysis. Part 1 will focus on identifying and describing the differences in use of social and health system services. Part 2 will result in the translation of these differences into dollar values, including the valuation of the intervention. Part 3 will focus on identifying and measuring the differences in quality of life for the children, parents and families. Part 4 will integrate the costing and quality of life information into a formal cost-utility analysis. Beginning with a budget impact analysis, Part 5 will examine the implications of the findings from an administrative and policy perspective.

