**Methods/Design:**

The Families First Edmonton Trial (FFE) tests four service integration approaches to increase use of available health and social services for families with low-income. It is a randomized, two-factor, single-blind, longitudinal effectiveness trial where low-income families (1168) were randomly assigned to receive either (1) Family Healthy Lifestyle plus Family Recreation service integration (Comprehensive), (2) Family Healthy Lifestyle service integration, (3) Family Recreation service integration, or (4) existing services. To be eligible families needed to be receiving one of five government income assistance programs. The trial was conducted in the City of Edmonton between January 2006 and August 2011. The families were followed for a total of three years of which interventional services were received for between 18 and 24 months. The primary outcome is the number of family linkages to health and social services as measured by a customized survey tool “Family Services Inventory”. Secondary outcomes include type and satisfaction with services, cost of services, family member health, and family functioning. Where possible, the measures for secondary outcomes were selected because of their standardization, the presence of published norming data, and their utility as comparators to other studies of low-income families. As an effectiveness trial, community and government partners participated in all committees through a mutually agreed upon governance model and helped manage and problem solve with researchers.

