### Aim of the study

This study focused on evaluating service integration approaches directed at increasing linkages between low-income families and services existing in their communities. The primary research question was:

What are the effects of three community-based service-integration approaches (Family Healthy Lifestyle, Family Recreation and Comprehensive), as compared to a control model (Existing Services), on the number of linkages that families initiate and maintain with established health and social services?

The design of the study enabled a thorough examination of several additional questions that are critical for understanding the influence of different service-delivery models on family linkages with established services, costs, and health. Secondary research questions included:

1. What are the relative effects of different service integration approaches on specific characteristics of family linkages to established service (e.g., type of service, satisfaction with), and how do the frequency and type of involvement change over time?

2. What are the costs to service systems of each of the service-integration approach over time?

3. What are the physical and psychosocial health outcomes of family members, over time, associated with each of these service integration approaches?

In order to effectively contribute to policy change, it was important to identify concurrent and antecedent variables related to linkage, cost, and health outcomes, and to estimate the likely impact of these variables [94,95]. Tertiary research questions included:

4. What is the intervening role of family functioning (family problem solving, communication, parenting, connections to community) between each of the four service integration approaches and linkage to services, cost, and health outcomes for family members, and how does this role change over time?

5. To what extent does sociodemographic profile (e.g., ethnicity, immigrant status, education, occupation, family type, level of income, sources of income, security of housing, number of children) influence the relation between each of the four service integration approaches and linkage to service, cost, and health outcomes, and how does this influence change over time?

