### Hypothesis

We hypothesized that low-income families who receive community-based service-integration (i.e., Family Healthy Lifestyle, Family Recreation and/or Comprehensive) would initially increase linkages to services, and that costs to service systems would decrease as improvements to physical and psychosocial health of family members are realized over time.

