## Methods/Design

### Study design

FFE is a randomized, single-blind, longitudinal effectiveness trial with a 2 by 2 factorial design with three integration groups and a control group. The study was conducted in the City of Edmonton between January 2006 and August 2011. The study employed a multi-prong strategy to recruitment. Eligible families were invited to the study through five source programs for low-income families. In addition, posters and invitation packages were available at community agencies and through service workers. Information about the study was presented at community events where eligible families could inquire for more information. All families who received the source programs during the recruitment period were invited to participate in the study. Families were randomized after baseline data collection using a 1:1:1:1 allocation ratio. Those who were assigned to the intervention groups received between 18 and 24 months of service integration intervention. All families were followed by researchers for a total of three years with a minimum of ten interviews for data collection: two at baseline, and two at year 1, year 2, and year 3, respectively.

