	**€ Primary Outcomes €**	
Linkages between low-income families and established services in their communities	Average number of times the family linked to services	Family Services Inventory (FSI)
Quality of life	Preference based measures	Visual Analogue Scale (EQ VAS) Australian Quality of Life (AQoL)

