### Data collection and management

Data were collected at baseline, prior to randomization, and then every 12 months for three years. One adult respondent per family was selected based on familiarity with the children. A focus child was randomly selected (using computer-generated randomized lists stratified by number of eligible children) amongst the children within the household at screening. When appropriate, children’s data were collected from the focus child. During data collection phase, follow-up data collections were conducted annually for all families. Research assistants who had established rapport with families since first contact arranged each data collection. Data collectors, blind to the group assignment, collected data during home visits. FFE researchers adopted a professional human resource model with a data collection supervisor who oversaw 29 data collectors and 36 interpreters. We adopted this model because (a) a number of our instruments are standardized measures requiring psychometric assessment skills, and (b) it enhanced our ability to attract and retain a staff with adequate credentials and experience. Most of our data collectors had completed or were working toward their Master’s degrees in a variety of health and social science fields. Data collectors were required to work evening and weekends, to be responsive to the schedules of the families, and all were rigorously trained on the data collection process, crisis management, and cultural sensitivity. A detailed manual of operations was available to the research assistants and data collectors at the coordinating office. Due to the volume of the data collected and to avoid fatigue of the primary participants, each data collection point consisted of two visits approximately 28 days apart. The 28 days lapse also allowed for a prospective collection of the services accessed by the family.

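### The primary model as listed has no approach-by-time term, so it gives one follow-up average per approach and cannot show the hypothesised initial rise or tell a fading effect from a sustained one

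*Protocol article*

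**What the plan says.** All references are to the protocol article.

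- **Model (Primary analysis).** The analysis is "linear regression including terms for the healthy family lifestyle and family recreation service-integration approaches, their interaction and, where appropriate, time (a repeated measure". Grammatically, the interaction is the one between the two approaches. Time is a conditional, separate term. The randomisation strata are added as covariates, and Poisson regression is the fallback for a skewed outcome.
- **Hypothesis.** Families offered service integration "would initially increase linkages to services, and that costs to service systems would decrease".
- **Primary question (Aim of the study).** It concerns effects "on the number of linkages that families initiate and maintain with established health and social services". A secondary question asks "how do the frequency and type of involvement change over time".
- **Primary measure (Table 1).** "Average number of times the family linked to services", with no visit named.
- **Exposure (Study design).** Intervention families "received between 18 and 24 months of service integration intervention". The Discussion adds that those who joined in the last six months of recruitment had at most 18 months.
- **Visits (Data collection and management).** "Data were collected at baseline, prior to randomization, and then every 12 months for three years". Under Outcome measures, the Family Services Inventory (FSI) covers roughly one month of use per annual visit, so each visit is a separate snapshot.

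**The concern.** A main effect of time moves all four groups up or down together. It does not let the difference between groups change from one visit to the next. With only the listed terms, each approach coefficient and the approach-by-approach interaction is a single number covering every visit entered.

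The design, however, changes exposure between visits, and the hypothesis is worded in terms of timing. A small pooled estimate could mean little effect at any time, or a useful effect during service that was lost afterwards. These lead to different policy conclusions, and the listed model cannot tell them apart. Switching to Poisson regression changes the scale but not this feature.

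**Working it through.** **1. Exposure at each follow-up visit** (service of 18 to 24 months; visits at 12, 24 and 36 months)

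| Visit | Families with 24 months of service | Families with 18 months of service |
|---|---|---|
| Month 12 | on service | on service |
| Month 24 | at the end of service | about 6 months off |
| Month 36 | about 12 months off | about 18 months off |

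One of the three follow-up visits is off service for everyone, and two of three are for families with 18 months. The model combines all three in one coefficient.

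**2. Does another planned analysis supply the time pattern for linkages?** The latent growth curve analysis under Other analyses is introduced for family functioning. Change over time in linkage frequency and type is a secondary question. Neither alters the terms of the primary model.

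**3. The plan's own power figure.** The Sample size section gives 300 per group, alpha 0.05, 25% attrition and power 0.72 at f = 0.10.

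- N after attrition = 4 × 300 × 0.75 = 900.
- Four-group F test: df = 3 and 896; noncentrality λ = N × f² = 900 × 0.01 = 9.
- Power = 0.709, close to the stated 0.72. At f = 0.25 power exceeds 0.999 (stated 0.99).

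This is a calculation for one measurement per family, so it serves as the single-visit benchmark.

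**4. Illustration of pooling.** Assumptions not in the article:

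- f = 0.10 applies at month 12.
- The three visits are equally weighted and complete.
- Any two visits of a family have the same correlation ρ, taken as 0.3 to 0.5.
- The effect follows one of the profiles below.

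Formulas: ā = mean of the profile; variance of a three-visit mean relative to one visit, v = (1 + 2ρ)/3; λ = 9 × ā²/v.

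- ρ = 0.3: v = 1.6/3 = 0.533.
- ρ = 0.5: v = 2/3 = 0.667.

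| Effect at 12 / 24 / 36 months | ā | λ (ρ = 0.3; 0.5) | Power (ρ = 0.3; 0.5) |
|---|---|---|---|
| Month 12 analysed alone | 1 | 9 | 0.71 |
| Full / full / none | 0.667 | 7.50; 6.00 | 0.62; 0.52 |
| Full / half / none | 0.500 | 4.22; 3.38 | 0.38; 0.30 |
| Full / full / full | 1 | 16.9; 13.5 | 0.95; 0.88 |

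Pooling loses power under either fading profile and gains it under a constant effect. The article gives no basis for choosing among these rows.

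**The case against.** The strongest reply has four parts.

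- **The list may not be complete.** The section speaks of a regression that includes certain terms, and of time where appropriate. This is a condensed article, and a fuller analysis plan may add approach-by-time terms. That possibility stands. The point therefore rests on the terms the article does list, which leave the effect constant across visits.
- **A follow-up average is a legitimate target.** The primary question covers maintaining as well as initiating linkages, and Table 1 speaks of an average number. This stands in part. A reader might infer that the model answers the wrong question, or that a null result would be uninterpretable. The article does not support either. A null pooled result with its confidence interval would still say that the average difference over follow-up is small.
- **The hypothesis may describe a sequence.** Linkages rise first and costs fall later, with no claim that the linkage effect disappears. This reading is possible. A reader might infer that a real effect will be diluted, but being off service need not mean no effect, since the aim is to connect families with services that already exist. The fading profiles above are not the plan's.
- **Baseline.** A reader might infer that the baseline visit, where no effect can exist, is averaged in as an outcome. Nothing in the article says so. It does not state how baseline enters, and no figure here relies on it.

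**Conclusion.** The point holds as a limitation of the listed primary model. It estimates an average follow-up difference, which partly meets the stated aim. It cannot display an initial increase, or separate initiation that fades from linkage that is maintained. This follows from the terms and holds whatever the true time course.

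The effect on power is conditional. Against 0.71 for month 12 alone, pooling gives 0.30 to 0.62 over the two fading profiles and 0.88 to 0.95 for a constant effect, under the assumed correlation and equal weighting.

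A reader might also conclude that month 12 must become the only primary estimate. The article does not require that. It would drop maintenance from the primary result and lose power if the effect persists. The choice is a real trade-off; what matters is that it is made openly and in advance.

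**What to change.** In the primary model:

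- Enter time as categorical (12, 24 and 36 months), with its interactions with each approach and with the approach-by-approach term.
- Allow for within-family correlation, for example with an unstructured or robust covariance.
- Use the baseline FSI value as a covariate, not as an outcome row.
- Report pre-specified approach effects at each visit together with the average over follow-up, which the same model yields.
- State before analysis which of these is primary. The Blinding section dates investigator unblinding to January 2012, so the choice should be recorded before linkage results are examined by group.

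The cost is plan wording and six further parameters beyond categorical time (3 approach terms × 2 time contrasts). No new data are needed. The price is precision: if the effect is constant, a single-visit estimate is weaker than the pooled average (0.71 against 0.88 to 0.95 in the illustration), which is a reason to keep the average in the report.

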### Outcome measures

The study aimed to determine which of the interventions impact accessibility in the most efficient and effective manner. Where possible, the measures were selected because of their standardization, the presence of published norming data, and their utility as comparators to other studies of low-income families.

The primary outcome, family linkage to health and social services, was measured using an innovative tool, “Family Services Inventory” (FSI). This tool was developed by a health economist, in consultation with FFE researchers. The FSI adopts a societal perspective and measures public and private consequences for families. The FSI was developed to maximize precision while minimizing patient burden and recall bias. A FSI toolkit comprised in-service training materials for data collectors, a user manual, a codebook, and a calendar (a memory aid to reduce recall bias). Annual data capture of resource use during the prior month was conducted in face-to-face interviews. Due to variations in scheduling interviews, resource use is normalized to the observation period (time between first and second visit). Characteristics of services and data allowing for costing of services were also collected in the FSI.

An overview of measures associated with the primary, secondary and intervening outcomes is found in Table 1.

**Table 1 T1:** Outcomes, measures, and instruments

**Outcome**	**Measure**	**Instrument**

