### Blinding

The data collectors and the investigators were blinded from the group assignments. The families, the service delivery workers and the research assistants were not blind to the group assignments at any point in the trial. Investigators were unblinded when the datasets were cleaned (January 2012).

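### The only fallback named for an untransformable, right-skewed primary outcome is Poisson regression, with no provision for variance above the mean; if it is used, the 95% intervals are likely too narrow

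*Protocol article*

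**What the plan says.** The primary outcome in Table 1 is "Average number of times the family linked to services", recorded with the FSI. The Outcome measures section adds that, because interview timing varies, "resource use is normalized to the observation period (time between first and second visit"). Under Data collection and management the two visits of each data point are about 28 days apart.

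The Primary analysis section sets the lead model: "The data will be analyzed using linear regression including terms for the healthy family lifestyle and family recreation service-integration approaches, their interaction". A term for follow-up year may be added to this model; the article's condition for it reads "where appropriate, time (a repeated measure"). The only covariates named besides the two intervention factors are the randomization strata: "The income group (Income Support vs. other source program) and the age of the focus child". The alternative is one sentence: "If the distribution of the primary outcome is right-skewed and cannot be transformed to a normal distribution, Poisson regression will be used". The section then promises: "Estimates and corresponding 95% confidence intervals will be reported".

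The Other analyses section leaves ethnicity, education, family type, number of children and similar variables to exploratory work. The model checks it names are residual, leverage and influence diagnostics. No section mentions a dispersion parameter, a negative binomial model, robust standard errors or an offset for observation time.

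**The concern.** Poisson regression fixes the variance of a count at its mean. If families differ in ways the model does not capture, the variance exceeds the mean, and model-based standard errors are too small by the square root of the ratio.

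The protocol gives its own reasons to expect this. Its tertiary questions (Aim of the study) ask how far number of children, family type, ethnicity, immigrant status, education and housing bear on linkage, yet none of these is in the primary model. Family size alone could spread a count taken at family level.

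A second problem concerns the response. A count divided by its observation time is no longer a Poisson variable, and its variance-to-mean ratio depends on the time unit chosen.

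At stake is the validity of the intervals and tests for the primary outcome whenever the fallback is used.

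**Working it through.** **The protocol's own figures.** The only nearby figures are the powers in the Sample size section, 0.72 at f = 0.10 and 0.99 at f = 0.25. With 4 × 300 × 0.75 = 900 families, a four-group F test at alpha 0.05 with noncentrality f² × 900 gives 0.709 and above 0.999. These agree with the stated values to within rounding or about one point. They assume a continuous outcome and say nothing about the Poisson branch. The document gives no mean, variance or dispersion for the FSI count, so the dispersion φ = variance/mean is an assumption below.

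**Step 1: fallback on the count, model-based standard errors.** The Poisson interval has 1/√φ of its correct width. Type I error at nominal 5% is 2 × [1 − Φ(1.96/√φ)], and coverage is one minus that.

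| Assumed φ | Relative width | Coverage | Type I error |
|---|---|---|---|
| 1 | 1.00 | 95% | 5% |
| 1.5 | 0.82 | 89% | 11% |
| 2 | 0.71 | 83% | 17% |
| 3 | 0.58 | 74% | 26% |
| 5 | 0.45 | 62% | 38% |

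**Step 2: simulation check.** The setting was a 2 × 2 design with 225 families per cell (300 less 25% attrition), gamma-Poisson counts with means of 3 to 10, a variable gap between visits, a rate per 28 days, and 1000 runs per setting. Model-based coverage was 95–96% at φ = 1, 83–86% at φ = 2, 75–77% at φ = 3 and 60–65% at φ = 5. With robust standard errors it was 94–95% throughout.

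**Step 3: would overdispersed data reach the fallback?** It applies only if transformation fails.
- Negative binomial counts with mean 8 and φ of 2 to 5 have skewness of about 0.75 to 1.4. After a square root this lies between about −0.1 and 0.1, with at most 4% zeros. Such data would most likely stay in linear regression.
- With mean 1 and φ = 3, the share of zeros is (1/φ)^(mean/(φ−1)) = (1/3)^0.5 = 58%. Skewness is still 1.0 after a square root and 1.1 after log(1 + count). Such data do reach the fallback.
- In 2000 simulated trials at mean 1 (225 per cell, raw count), type I error with model-based standard errors was 16%, 26% and 39% at φ = 2, 3 and 5. With robust standard errors it was 5–6%.

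The inflation in Step 1 therefore also holds for data that trigger the fallback.

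**Step 4: normalised rate as the response.** Let T be the observation period in the chosen unit. The rate count/T has mean μ/T and variance φμ/T², so its variance-to-mean ratio is φ/T.
- Per 28 days, T ≈ 1 and the ratio is φ, so Step 1 applies.
- Per day, T ≈ 28 and the ratio is φ/28. At φ = 5 that is 0.18, and the model-based interval is far too wide.

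Simulation with true Poisson counts (φ = 1, mean 5) gave 96.5% coverage per 28 days and about 100% per day. The raw count with a log-time offset gave 95–96%.

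**The case against.** The strongest reply has four parts.

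1. *The branch is conditional.* Linear regression leads, and Poisson enters only if transformation fails. This stands: a reader might infer that the fallback is the likely route, and the document does not support that. Moderately large overdispersed counts would be normalised by a square root (Step 3). Low-mean data with many zeros would not.

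2. *Silence is not a choice.* Robust standard errors, an offset and the handling of repeated visits may be set out in an analysis plan that is not shown. This stands in part. It would be wrong to say that the plan rejects such measures or commits to model-based standard errors. But the article does name the model family, so using a negative binomial model would mean departing from its sentence.

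3. *The dispersion is assumed.* This stands: at φ = 1 nothing is wrong. Reaching the fallback does not prove overdispersion either, since a low mean alone produces skew that no transformation removes. The case for φ above 1 rests on the family characteristics left out of the model.

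4. *A normalised rate need not make intervals too narrow.* This stands, as Step 4 shows. Normalising could also be done through an offset, so it is not certain that a rate would be the response.

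Two further inferences are tempting and not supported. One is that the choice of model is open to selection, because "Investigators were unblinded when the datasets were cleaned (January 2012"). The rule depends on the shape of the outcome distribution, which can be judged with the arms pooled, and nothing says that group results inform it. The other is that transforming the outcome is an error because costing needs means. Transformation is conventional, and the costing is described as a separate analysis.

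**Conclusion.** The point holds in a limited form. The protocol fixes Poisson regression as the sole fallback for the primary outcome and provides nothing for variance above the mean, which its own research questions make likely. If that fallback is applied to the count with model-based standard errors, type I error is about 17%, 26% or 38% at an assumed φ of 2, 3 or 5, with coverage of 83%, 74% or 62% for a nominal 95% interval.

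These sizes rest on three conditions: that the fallback is triggered, that standard errors are model-based, and that φ lies in the assumed range. The document settles none of them. If a period-normalised rate is the response, the direction of the error depends on its unit. The lead linear regression is not called into question.

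**What to change.** Replace the fallback sentence. If the outcome is right-skewed and cannot be transformed, fit either a negative binomial regression, or a Poisson regression with robust standard errors clustered on family, to the raw FSI count. Use log(days between visits) as the offset, and keep the two intervention factors, their interaction, time where it applies, and the two strata covariates. If the negative binomial option is chosen with repeated visits, state how within-family correlation is handled.

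The cost is a sentence or two, with no new data and standard commands in common software. Intervals will be wider than plain Poisson would show, by √φ: about 1.4, 1.7 or 2.2 times at φ = 2, 3 or 5. At φ = 1 they should be almost unchanged. The lead linear regression and the transformation step need no change.

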### Sample size

Projecting a moderate (f = 0.25) and even a small (f = 0.10) intervention effect size (mean divided by standard deviation), given an alpha of 0.05 and a 25% attrition rate, the study proposed an initial sample size of 300 families per group to detect any significant difference between the four groups (power was 0.99 and 0.72, respectively). The study randomized approximately 290 families to each group. The overall alpha value was not controlled for multiple comparisons. No interim analyses were planned.

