### Losses and exclusions after randomization

As indicated in Figure 1, during the process participants could either withdraw (i.e., lost to follow-up) or be ‘dormant’ for some of the data collection points (i.e. unavailable). At 36 months we were able to collect data from 748 families; data from 414 families were lost (135 Existing Services, 88 Family Recreation, 110 Family Healthy Lifestyle, and 91 Comprehensive). Table 2 shows reported reasons for withdrawal.

**Table 2 T2:** Losses and exclusions

**Reasons for withdrawal**	**Before randomized**	**After randomized**	**Reasons for withdraw (count)**
Not interest in	55	18	73
Too busy/No time	47	40	87
Move out of study area	10	88	98
Family circumstances	8	9	17
Problems with research	6	4	10
Problems with randomized design	5	-	23
Problems with services allotted	-	18	18
Health	3	5	8
Kids not interests in	3	1	4
Too much time past since last contact	3	0	3
Cultural differences	1	0	1
Stigmatization	0	1	1
Unknown	18	5	23
**Grand Total**	**159**	**189**	**366**

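### The primary model adjusts for the randomisation strata but does not list the family's own baseline linkage rate, so available precision is left unused

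*Protocol article*

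**What the plan says.** The Primary analysis section describes a linear regression, with Poisson regression as the fallback for a right-skewed outcome that cannot be transformed. The terms named are the two service-integration factors, their interaction and, where appropriate, time as a repeated measure. Two covariates follow: income group and "the age of the focus child corresponding to strata variables in randomization will be included in the model". Baseline service linkage is not named there, nor among the exploratory variables under Other analyses, and change from baseline is not mentioned anywhere.

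The baseline value should exist. Data collection and management states: "Data were collected at baseline, prior to randomization, and then every 12 months for three years". The same section says that every data collection point had two visits about 28 days apart, which let services be recorded prospectively. Outcome measures says that resource use is normalised to the time between the two visits. Allocation to experimental group and implementation says that envelopes were opened after baseline collection was complete.

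On size, the Sample size section reads: "Projecting a moderate (f = 0.25) and even a small (f = 0.10) intervention effect size", "given an alpha of 0.05 and a 25% attrition rate", "the study proposed an initial sample size of 300 families per group", and "power was 0.99 and 0.72, respectively".

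**The concern.** The outcome's own pre-randomisation value is usually a useful covariate in a trial with a continuous or count outcome. Here it comes from the same instrument and the same two-visit window as the follow-up values, yet the stated model spends its covariates only on the strata. By the plan's own figure, power for the small effect is 0.72, so unused precision bears on whether a small effect would be detected and on the width of the reported confidence intervals.

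A second question is how the time term is meant. If the baseline wave is an outcome row, the listed terms do not let the intervention effect be absent at baseline and present afterwards.

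**Working it through.** **Inputs.** From Sample size: alpha 0.05; f = 0.25 and 0.10; 300 families in each of four groups; 25% attrition; stated power 0.99 and 0.72. Analysable N = 4 × 300 × 0.75 = 900. Not in the document, so assumed: the baseline-to-follow-up correlation ρ of the linkage rate, taken from 0.2 to 0.7.

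**Step 1: reproduce the plan's power.** Four-group omnibus F test, df 3 and N − 4 = 896, noncentrality λ = N f².
- f = 0.10: λ = 900 × 0.01 = 9; power 0.709 (stated 0.72).
- f = 0.25: λ = 900 × 0.0625 = 56.25; power above 0.999 (stated 0.99).

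Both agree within two points. Other readings at f = 0.10 do not: 0.839 without attrition (N = 1200), 0.850 for a one-degree-of-freedom factor effect at N = 900, and 0.564 for a pairwise comparison (d = 0.2, 225 per arm). The stated figure is therefore consistent with an omnibus test after attrition without a baseline covariate.

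**Step 2: add the baseline rate.** In linear analysis of covariance, residual variance is multiplied by 1 − ρ², so λ becomes 9/(1 − ρ²), with one fewer residual degree of freedom.

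| ρ (assumed) | 1 − ρ² | SE multiplier | λ | Equivalent unadjusted N | Power, f = 0.10 |
|---|---|---|---|---|---|
| no covariate | 1 | 1 | 9 | 900 | 0.709 |
| 0.2 | 0.96 | 0.980 | 9.38 | 938 | 0.729 |
| 0.3 | 0.91 | 0.954 | 9.89 | 989 | 0.754 |
| 0.4 | 0.84 | 0.917 | 10.71 | 1071 | 0.790 |
| 0.5 | 0.75 | 0.866 | 12 | 1200 | 0.838 |
| 0.7 | 0.51 | 0.714 | 17.65 | 1765 | 0.955 |

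At ρ = 0.5, 900 adjusted families are worth 900/0.75 = 1200 unadjusted ones, which offsets the planned attrition.

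**Step 3: several follow-up waves.** For the mean of three follow-ups with equal correlation ρ between all waves, the variance (in units of one wave) is (1 + 2ρ)/3 unadjusted and (1 + 2ρ)/3 − ρ² adjusted. At ρ = 0.3 this is 0.533 against 0.443 (ratio 0.83); at 0.5, 0.667 against 0.417 (0.625); at 0.7, 0.800 against 0.310 (0.39). Averaging follow-ups does not make the baseline redundant.

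**Step 4: baseline as an outcome wave.** Suppose baseline is one of four outcome rows and the intervention enters only as listed, with no intervention-by-time term. With complete data and equal correlation between waves, the fitted effect is the mean effect over the waves. For a constant post-baseline effect δ it is (0 + δ + δ + δ)/4 = 0.75δ, and this is the same at ρ = 0.3, 0.5 and 0.7.

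**The case against.** The strongest reply is that this is a condensed article. It says that the strata variables will be in the model, not that nothing else will be, and a full analysis plan may add baseline linkage. That possibility stands. Still, the article names the model's terms and covariates, and a reader who implements them would leave the baseline out.

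A second reply is that the repeated time term already brings the baseline in. The wording allows that reading, but time enters only where appropriate and no intervention-by-time term is given, so step 4 applies. Both readings need a repair.

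Third, the size is assumed. The document gives no correlation and no SD, and the predictor is a roughly 28-day rate measured one to three years earlier. At ρ = 0.2 the gain is about two points. The factor 1 − ρ² belongs to linear regression and does not carry over directly to the Poisson fallback. All of this stands.

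Some stronger inferences are not supported:
- **That the trial's power is 0.62.** The article reports: "At 36 months we were able to collect data from 748 families". At N = 748 unadjusted omnibus power for f = 0.10 is 0.619, and 0.665, 0.757 or 0.909 with adjustment at ρ = 0.3, 0.5 or 0.7. But Statistical methods plans last observation carried forward. With all 1168 families analysed, nominal power is 0.83, although carried-forward values may dilute the effect. Neither N shows the stated power to be wrong.
- **That there is a shortfall on every test.** For a one-degree-of-freedom factor effect of f = 0.10, which is a different effect from the omnibus f, unadjusted power is already 0.85 at N = 900.
- **That adjustment corrects differential dropout.** It can reduce only the part of dropout bias related to baseline linkage, and the document does not show that dropout depends on it. Arm-level loss rates cannot be computed reliably either: the four losses under Losses and exclusions sum to 135 + 88 + 110 + 91 = 424, not the stated 414, and 748 + 414 = 1162, not 1168.
- **That number of children must move into the primary model.** It is listed as exploratory, nothing in the document sizes its effect, and it may stay there.

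**Conclusion.** The point holds as one of efficiency. The stated primary model omits the outcome's own pre-randomisation value, which the article indicates was collected. Randomisation keeps the comparison without it valid, and the power statement reproduces. At f = 0.10 and N = 900, the gain in omnibus power is about 2 points at ρ = 0.2, 4 to 5 at 0.3, 13 at 0.5 and 25 at 0.7; power passes 0.80 between ρ = 0.4 and 0.5. These figures assume linear analysis of covariance and a correlation that the document does not give. If baseline is meant to be an outcome wave, the listed terms would shrink a constant post-baseline effect to three quarters of its size, given complete data and equal correlation between waves. A reader might infer that the analysis is biased or the trial mis-sized by this omission; the document supports neither. The change is worth making, but the conclusions do not stand or fall on it.

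**What to change.** State one of two models for the primary outcome:
- baseline FSI linkage rate as a covariate (on the log scale if Poisson regression is used), with only the follow-up waves as outcomes; or
- a constrained longitudinal model with all waves as outcomes, a common baseline mean across groups, and intervention-by-time terms.

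Do the same with the baseline score for each secondary outcome measured at baseline. Say explicitly whether baseline is an outcome row.

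The cost is a few lines of text and no new data. Timing matters, however: Blinding says that investigators were unblinded in January 2012. If the term is added after that date, report it as a post-unblinding change and present the model without it as a sensitivity analysis.
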